## Abstract

**Background:**

Pulmonary fibrosis (PF) is caused by a heterogeneous group of diseases, with a high inter-individual variability in disease trajectory. Identifying disease progression in patients with PF has impact on clinical management decisions. However, strategies to early identify and predict disease progression for these patients are currently lacking. In this study, we aim to assess long-term FVC change in patients with PF measured with home spirometry, and evaluate the feasibility of a multinational patient-led registry in PF. In addition, we will assess validity of patient-reported outcomes (PROMs) for the different subgroups of patients with PF.

**Methods:**

In this international, prospective, multicenter, observational study, we aim to include 700 patients across seven European countries. Patients will monitor their disease course for a period of two years using an online home monitoring program (I-FILE), which includes home spirometry, pulse oximetry, and PROMs. Results will be directly sent to the hospital via the online application. Patients will be asked to perform daily home spirometry and pulse oximetry in the first three months, followed by once weekly measurements for a period of two years. PROMs will be completed in the online I-FILE application every six months, including the King’s brief Interstitial Lung Disease Health Status, The EuroQol five dimensions five-level, Visual Analogue Scales on cough, dyspnea, fatigue and general complaints, Leicester Cough Questionnaire, Fatigue Assessment Scale, Work Productivity and Activity Impairment Questionnaire, Global Rating of Change Scale, and Living with Pulmonary Fibrosis questionnaire.

**Discussion:**

This study will provide much needed insights in disease trajectories of the different subgroups of patients with PF. Simultaneously, the I-FILE study will yield valuable information on the use and feasibility of home-based data collection. This international patient-led registry will facilitate trans-border collaboration to further optimize care and research for patients with PF.

*Trial registration:* The study was registered on the 12th of March 2020 in the International Clinical Trial Registry, www.clinicaltrials.gov; Identifier: NCT04304898.

**Supplementary Information:**

The online version contains supplementary material available at 10.1186/s12890-023-02336-4.

## Background

Pulmonary fibrosis (PF) is a manifestation of different interstitial lung diseases, characterized by fibrotic remodeling of the lung, leading to pulmonary function loss [1, 2]. Disease course and prognosis of PF widely vary between individuals and due to different underlying etiologies [3–6]. Symptoms such as cough, dyspnea, impaired exercise tolerance, fatigue, anxiety and depression, significantly impair health-related quality of life (HRQOL) of patients with PF [7–9]. With appropriate and timely management, some forms of PF have the potential for stabilization or, in a subgroup with more inflammatory disease, even improvement [1]. However, a subset of patients have a progressive disease course, characterized by increasing symptoms, decline in pulmonary function and HRQOL, and ultimately early mortality [2–6, 10, 11]. With a median survival of two to three years without treatment, idiopathic pulmonary fibrosis (IPF) is the most progressive form of PF [12]. Nevertheless a group of patients with other forms of pulmonary fibrosis have a similar rapidly progressive disease course. New guidelines have introduced the term progressive pulmonary fibrosis (PPF) for this progressive phenotype of PF in patients with a diagnosis other than IPF. Due to the heterogeneity of PF, predicting the disease course for individual patients remains challenging. Especially for the more rare and ultra-rare forms of PF, detailed data about disease behavior and trajectory is currently lacking. Therefore, more comprehensive data for the different forms of PF is needed.

Nowadays, identifying disease progression has direct treatment implications. Anti-fibrotic medication is the mainstay of treatment for IPF, as it reduces pulmonary function decline and prolongs survival [13–15]. More recently, studies demonstrated beneficial effects of the anti-fibrotic medications Nintedanib and Pirfenidone for PPF [16–19]. This has led to the approval of anti-fibrotic treatment (Nintedanib) for this patient group [16, 17]. However, data on timing of treatment initiation, and combination with immunomodulatory treatment in patients with PPF are still scarce. Moreover, real-life data about adverse events and effectiveness in patients with comorbidities or severely impaired pulmonary function, and not eligible for clinical trials, are currently also not available.

In current guidelines, disease progression is defined by a combination of worsening symptoms, radiological and/or physiological progression [20]. In-hospital forced vital capacity (FVC) trends are accepted as current standard to monitor physiological disease progression. Nevertheless, FVC measurements have an inherent variability and are usually measured at low frequency during visits to the pulmonologist, possibly delaying detection of disease progression, and consequently, management decisions. Online home monitoring, using eHealth technology, enables more frequent measurements of pulmonary function and symptoms by patients at home, which will help to get a more detailed overview of disease course in individual patients. Home monitoring in PF has gained increasing interest in recent years, with studies demonstrating its feasibility and reliability in this patient population, despite technical and analytical issues [18, 21–25]. Results of an international survey revealed that ILD healthcare providers are positive towards the use of online home monitoring for daily care, but also for research and registry purposes [26]. A large online multinational patient registry could be a major step towards the better understanding of PF heterogeneity, and thus improve its management. eHealth technology can help lift the burden of frequent data collection, and provide a more practical way of data collection. It could facilitate trans-border collaboration and pooling of data in a patient registry, as distances are bridged online.

In the I-FILE study, we aim to gain more insights in disease behavior and response to treatment in patients with PF using online home monitoring. In addition, we will evaluate the feasibility of a patient-led registry in PF.

## Methods

### Objectives

The main aim of this study is to assess long-term FVC change in patients with PF measured with home spirometry. Our secondary aims are to evaluate feasibility, adherence, patient and healthcare provider experiences and satisfaction, and to assess validity existing PROMs in patients with PF.

### Study design and participants

The I-FILE study is an ongoing prospective multicenter, multinational, observational pilot study (NCT04304898). Patients with ILD, newly diagnosed in a multidisciplinary discussion (MDD), and PF on high-resolution computed tomography (HRCT), will be included in both community and tertiary centers in Belgium, France, Germany, Greece, the Netherlands, Norway and The United Kingdom. The trial is currently underway, and patients are being recruited. We aim to include approximately 700 patients in total. Patients will be considered newly diagnosed, when the diagnosis has been established within six months before inclusion in an MDD. In addition, patients should be either treatment naïve or have received treatment for their PF for a maximum of one month before inclusion. For more detail, inclusion—and exclusion criteria are shown in Table 1.

**Table 1 Tab1:** Inclusion and exclusion criteria of the I-FILE study

Inclusion criteria	Exclusion criteria
Newly diagnosed patients with ILD and PF on HRCT Pulmonary fibrosis present on HRCT according to current guidelines, confirmed by a thoracic radiologist at the MDD [20] MDD diagnosis ≤ 6 months before inclusion Treatment for ILD ≤ than 1 month	Not able to speak, read or write in the native language of the country where the patient is included
	Not able to comply to the study protocol, according to the judgement of the investigator and/or patient
	No access to the internet

*ILD* Interstitial lung disease*, PF* Pulmonary fibrosis*, MDD* Multi-disciplinary discussion*, HRCT* High-resolution computed tomography

### Study procedures

In the I-FILE study, patients will use an online home monitoring program, consisting of the online I-FILE application integrated with home spirometry, for two years. If eligible for participation, patients will receive information on the I-FILE study by their treating physician. Written informed consent will be obtained before start of the study. At time of inclusion, patients will be instructed on the use of the I-FILE application and spirometer. Patients will perform once daily home spirometry and oximetry measurements for the first three months, followed by once weekly measurements (three consecutive home spirometry and one oximetry measurement). In addition, patients are asked to complete patient reported outcomes (PROMs) in the online application every six months. Permission will be asked separately to reassess medical records and online data for another five years after the end of the study. After two years, patients will be asked to fill in a twelve-item survey on their experiences with the home monitoring program. After two years, patients are offered the possibility to continue using the system if they wish.

Baseline characteristics, such as patient demographics, clinical characteristics, medication, data on HRCT, histology, comorbidities, hospital-based pulmonary function tests, and laboratory results will be collected at time of inclusion. An overview of the data collection is shown in Additional file 1: Table S1. No adjustments will be made in regular care of participating patients. Every six months, during outpatient clinic visits, patients will be asked about hospitalizations, changes in medication use and side-effects of medication for PF. Hospital-based spirometry, consisting of FVC, Forced Expiratory Volume in 1 s (FEV1), and diffusion capacity of the lung for carbon monoxide (DLCO), will be performed according to international guidelines. An overview of the study flow is shown in Fig. 1. After completion of the study, healthcare providers and research staff are asked to fill in a survey on their opinions and experiences with the home monitoring program in an online twelve item survey.

**Fig. 1 Fig1:**
[figure not shown]
Study Flow I-FILE study. Home monitoring of patients with progressive pulmonary fibrosis using home spirometry, pulse oximetry, and patient reported outcome measures (PROMs)

### I-FILE application

I-FILE is an online eHealth application (Curavista, Gezondheidsmeter, Geertruidenberg, the Netherlands) (www.i-file.app). This application has been successfully used in earlier (multi-center) home monitoring studies [23–24]. At time of inclusion, all patients will receive a password-protected personal account, and the I-FILE application will be installed on their smartphone or tablet in their native language. If patients do not own a smart device, they will be provided with a tablet computer for the duration of the study. The I-FILE application includes home spirometry, pulse oximetry, online completion of questionnaires and symptom scales, possibility for eConsultation with healthcare providers, an option for private notes for the patients, and a real-time overview of results over time (Fig. 2).

**Fig. 2 Fig2:**
[figure not shown]
Digital platform of the I-FILE study

At first login, patients will be asked to tick a box to consent that their data can be stored in a database and used for research purposes; they can recall this consent at any time. All study results will be encrypted and directly sent to a secured and approved server (Gezondheidsmeter, the Netherlands), which has the highest European Certification for safety (NEN7510 and ISO27001), is CE-marked and complies with all safety regulations (i.e. General Data Protection Regulation).

Patients will be provided with an instruction manual on paper for the use of the I-FILE application. They will find additional information about the study on the I-FILE website, which includes animated instruction videos on the I-FILE study and the use of the spirometer. In addition, both patients and research staff will have access to a technical helpdesk in their native language.

Healthcare providers and research staff will receive a password for an online dashboard with an overview of all participating patients from their center. They will have real-time access to all patient data, except for the part with private notes. Some hospitals will have direct access to the I-FILE platform via the electronic patient file in their hospital. The data will be made available to all collaborating investigators and patient associations for different research questions and post-hoc data analyses.

Patients will receive automated reminders if measurements are not performed according to the study protocol. In case of repeated missing measurements, research staff will receive automated alerts with instructions to contact the patient. In addition, healthcare professionals are instructed to check the results of the included patient on a regular basis. Healthcare providers do not receive automated alerts in case of changes in pulmonary function, oxygen saturation or PROMs.

### Home spirometry and pulse oximetry

Home spirometry and oximetry measurements will be performed using a Bluetooth-enabled validated, CE-marked home spirometer (Spirobank Smart or Spirometer OXI MIR, Italy). Patients will be instructed by a trained member of the research team and will perform a minimum of three test blows on the home spirometer to ensure reliability of the home spirometry results. Home spirometry measurements will be considered reliable if the highest FVC value deviates less than ten percent from the in-hospital FVC value conducted at baseline, and if the difference between two consecutive measurements is less than 150 ml [28]. Patients are instructed to perform home spirometry approximately at the same time to reduce variability [29]. Oxygen saturation is measured in the subgroup of patients who use the Spirometer OXI, by placing their finger on the integrated sensor for 30 s. All measurements will be directly sent to the research team with a personal 5-digit code. Both patient and research team will have real-time access to the flow-volume loops, quality assessment of the measurements, and a trend line of the FVC and the FEV1 over time.

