### Endpoints and statistical analysis

We will evaluate absolute changes in FVC (L and % predicted) measured with home spirometry, and oxygen saturation (%) measured with pulse oximetry, from baseline to 6, 12, and 24 months. These changes will be analyzed using a linear mixed model with disease and country as fixed effects. Repeated measurements within a patient will be corrected by random effects (intercepts or slopes, depending on the data). This model corrects for random missing data. Possible non-linear evolutions and correlations between subsequent observations will be accounted for through flexible modeling of the time variable and structured error terms in the variance–covariance matrix of the random effects. Absolute in-hospital FVC changes between baseline, 6, 12 and 24 months (L and %predicted), HRQOL, and symptom scores will also be assessed with linear mixed models. The correlation of home and hospital spirometry will be analyzed by calculating Pearson’s correlation coefficient, taking the individual mean FVC changes for each patient into account. Results will be used to optimize analytical methods to deal with outliers and missing data. Besides, a delta (Δ) change will be computed for HRQOL and symptom changes from baseline to 6, 12 and 24 months. Furthermore, we will use group based trajectory modeling and joint models to predict outcomes in individual patients (e.g. respiratory related and all cause hospitalizations, disease progression, and mortality) To measure time to decline in HRQOL, we will use the minimal clinically important difference (MCID) for all individual patient reported outcomes. Joint models will be used to assess time to reach the MCID. Adherence to the home monitoring program will be assessed by evaluating the completeness of data. The total number of measurements from each participant will be divided by the number of expected measurements, for pulmonary function as well as PROMs. The incidence rate of new oxygen prescription, non-elective hospitalization (respiratory and all cause), mortality (all cause and respiratory-related) will be summarized descriptively by diagnosis cohort. Disease progression will be defined according to the guideline criteria and its individual components, and will be compared with criteria used in different trials [16–18, 20]. We will also perform analyses with different cut-off values for FVC and DLCO. Multivariate logistic regression, ROC curve analysis and a multivariate Cox proportional hazards model will be used to identify possible predictive factors for disease progression and/or mortality. Differences between countries will be analyzed with ANOVA. If possible, HRQOL questionnaires will be validated for the different forms op PF by assessing internal consistency, discriminative ability, concurrent validity, and responsiveness. Patient and healthcare providers satisfaction with the home monitoring program will be summarized descriptively. An overview of the pre-specified endpoints is shown in Table 3.

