
**Table 3 Tab3:** Prespecified endpoints of the I-FILE study

*Primary endpoint*
Absolute FVC change measured with home spirometry from baseline to 6, 12 and 24 months (in % and L)
*Secondary endpoints*
Absolute FVC change measured with in-hospital spirometry between baseline and 6, 12 and 24 months (in % and L) Absolute DLCO change measured with in-hospital spirometry between baseline and 6, 12 and 24 months (in % and L) Change in oxygen saturation from baseline to 6, 12 and 24 months (in %) Correlations between home and hospital spirometry Adherence to daily and weekly home spirometry HRQOL and symptom changes between baseline, 6, 12 and 24 months Time to change in HRQOL Correlations between pulmonary function tests and PROMs at all time points Internal consistency, discriminative ability, concurrent validity, and responsiveness of PROMs in individual diseases Hospitalizations (all cause and respiratory related) Mortality Percentage of patients with disease progression Identification of markers for disease progression or death Percentage of patients with new oxygen prescription Differences in outcomes between countries Differences in outcomes between subgroups of PF Healthcare provider and patient satisfaction and experience with the online application

*FVC* Forced vital capacity, *HRQOL* Health related quality of life, *PROMs* Patient reported outcome measures, *PF* Pulmonary fibrosis

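### Home oximetry is scheduled for all patients but measured only in users of one device, and the SpO2 change analysis is not linked to new oxygen prescription

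*Protocol article*

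**What the plan says.** Two places in the protocol article give the oximetry schedule without any limit by device. The Methods part of the abstract says: "Patients will be asked to perform daily home spirometry and pulse oximetry in the first three months, followed by once weekly measurements". The section on study procedures says: "Patients will perform once daily home spirometry and oximetry measurements for the first three months", and then sets a weekly routine that includes one oximetry reading.

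The section on home spirometry and pulse oximetry allows two spirometers, the Spirobank Smart and the Spirometer OXI, and states: "Oxygen saturation is measured in the subgroup of patients who use the Spirometer OXI". The reading is taken with a sensor built into that device. The article does not say who receives which device, or how many receive the OXI.

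Table 3 has a secondary endpoint that begins "Change in oxygen saturation from baseline to 6, 12 and 24 months (in"; the unit follows. Neither that row nor the text on endpoints and statistical analysis names a subgroup. For home FVC and SpO2 together, that text says: "These changes will be analyzed using a linear mixed model with disease and country as fixed effects". It adds patient-level random effects and says that the model deals with randomly missing data.

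A separate row of Table 3 reads: "Percentage of patients with new oxygen prescription". The analysis text gives this event an incidence rate, summarised descriptively by diagnosis.

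**The concern.** There are two separate problems with the same endpoint.

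The first is who is measured. If only OXI users have a sensor, the other patients have no SpO2 value at any time, baseline included. A reader of the abstract and Table 3 would take the SpO2 result as describing the whole cohort ("We aim to include approximately 700 patients in total"), when it can describe only one device group of unknown size.

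The second is what is measured once a patient starts oxygen. The study expects some patients to do so, because it counts them. A reading on supplemental oxygen is a different quantity from one on room air: it can rise while the disease advances. If both kinds enter one change model without distinction, decline is hidden in the patients who worsen. The statement on missing data does not help, because these readings are observed.

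**Working it through.** **The passages side by side**

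| Place in the article | Who has oximetry |
|---|---|
| Abstract, Methods | patients in general |
| Study procedures | patients in general |
| Home spirometry and pulse oximetry | Spirometer OXI users only |
| Analysis text and Table 3 | no limit stated |

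The third row cannot stand with the first two unless every patient receives the OXI, and the word subgroup rules that out. The article mentions no separate oximeter.

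The article gives no SpO2 calculation, so there is no figure to reproduce. It also gives no OXI share, no rate of starting oxygen and no expected SpO2 change. Apart from the 700 patients, every input below is an assumption used to show a range.

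**Precision.** Let s be the share with the OXI. Patients with data = 700 × s, and the standard error relative to measuring all 700 is √(1/s).

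| s | Patients | SE multiple |
|---|---|---|
| 10% | 70 | 3.16 |
| 25% | 175 | 2.00 |
| 50% | 350 | 1.41 |
| 75% | 525 | 1.15 |

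**Reading the subgroup result as a cohort result.** Error = (1 − s) × (mean change in OXI users − mean change in the others). With a difference of 1 point, it is 0.75, 0.50 or 0.25 points at s = 25%, 50% or 75%. The direction is unknown, and the error is zero if device use is unrelated to the course of SpO2.

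**Readings on new oxygen.** Let p be the share who start oxygen, d_s their underlying decline and d_n the decline in the others, in points. Suppose oxygen returns the starters' readings to baseline.

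- True decline = p·d_s + (1 − p)·d_n
- Observed decline = (1 − p)·d_n
- Understatement = 1 − observed/true

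Each cell gives true decline, observed decline and understatement.

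| p | d_s = 2, d_n = 2 | d_s = 4, d_n = 1 | d_s = 6, d_n = 1 |
|---|---|---|---|
| 5% | 2.00, 1.90, 5% | 1.15, 0.95, 17% | 1.25, 0.95, 24% |
| 10% | 2.00, 1.80, 10% | 1.30, 0.90, 31% | 1.50, 0.90, 40% |
| 20% | 2.00, 1.60, 20% | 1.60, 0.80, 50% | 2.00, 0.80, 60% |
| 30% | 2.00, 1.40, 30% | 1.90, 0.70, 63% | 2.50, 0.70, 72% |

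The understatement equals p·d_s divided by the true decline. If oxygen restored only half of the starters' fall, every percentage would halve. If all readings were taken on room air, it would be zero.

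**The case against.** The strongest reply is that this is a condensed article. Rules on room-air readings, analysis sets and the handling of readings after oxygen starts may sit in the full protocol or the SAP, which are not shown. The device section could also be read as qualifying the general schedule. And SpO2 is a secondary endpoint of an observational pilot study. Part of this stands: silence on room air is not in itself an error, and the primary endpoint is untouched. But the article contradicts itself on who is measured, and it states the SpO2 model and endpoint without the device limit or a link to oxygen start. An unseen document does not cure that.

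Four stronger readings are tempting, and the documents support none of them.

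- A reader might infer that oxygen therapy is ignored. It is not: new prescription is a prespecified endpoint with its own incidence rate. Only the link to the SpO2 analysis is absent.
- A reader might infer that devices are allotted non-randomly and that OXI users are unrepresentative. No allotment rule is given, so this is a risk and not a fact. If allotment followed country, the country term would adjust for part of it, but it could say nothing about a country without OXI users.
- A reader might infer that the device restriction biases SpO2 toward no decline. That direction comes only from readings on oxygen.
- A reader might want a device term in the models. Among OXI users it would be constant and could not be estimated. For home FVC no device bias is shown, and a stable device offset cancels in within-patient change.

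It can also be objected that stopping at oxygen start changes the question. That is true, and it is why the all-readings result should be shown as well.

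**Conclusion.** The contradiction over who has oximetry is certain from the text, and the SpO2 endpoint as worded covers patients who can have no data.

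The second part is conditional. If readings taken on newly started oxygen enter the stated model, decline is understated in the patients who worsen. The documents do not size this. The 5% to 72% range assumes that 5% to 30% start oxygen, that starters fall 2 to 6 points and the others 1 or 2, and that oxygen fully restores the readings. It shows that the effect could be anything from small to dominant; it is not an estimate for this study.

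The consequence is confined to a secondary endpoint and to statements that rest on it, such as SpO2 comparisons between countries or disease groups. The point is worth correcting before analysis because the correction is cheap.

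**What to change.** 1. Reconcile the abstract and the study procedures with the device section by stating that oximetry applies to Spirometer OXI users. Put the same limit on the SpO2 endpoint in the analysis text and in Table 3.
2. Report how many patients use the OXI, and compare their baseline profile and country mix with those of the other patients. Limit the SpO2 conclusion to OXI users.
3. Analyse SpO2 change using readings up to the date of new oxygen prescription, or use all readings with a time-varying on-oxygen indicator. Optionally, treat oxygen start and death as events in the joint models that the article already plans. This would help because stopping at oxygen start removes follow-up selectively from patients who worsen.
4. Show the all-readings result alongside.

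The first two items cost wording and one descriptive table. The third needs a date of oxygen prescription. The six-monthly questions listed in the study procedures do not name oxygen, but an incidence rate already calls for some record of when it began. The price is fewer SpO2 readings after oxygen starts and, if readings stop there, an estimate that refers to SpO2 before supplemental oxygen and must be labelled so. Nothing in patient care changes.
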